#### 4.8. End of Study

The End of the study is when all participants have completed all scheduled assessments and all questionnaire/data items have been completed and for those undertaking it, the semi-structured interview has been undertaken.

### 5. Safety

Adverse event reporting will be conducted in accordance with the Sponsor's Adverse Event Reporting Procedures. A clinical co-investigator will be responsible for determining the causality and seriousness of adverse events, as well as all non-serious adverse events that are either deemed to be related to participation in the research or result in withdrawal from the WBV programme or study.

Serious adverse events are defined as any untoward medical occurrence that results in one of the following criteria: results in death; is life threatening; requires unplanned or prolonged hospitalization; results in persistent or significant disability or incapacity, or; results in a congenital abnormality or birth defect. Non-serious events are defined as any untoward medical occurrence that does not fulfil any of the serious adverse event criteria.

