## 4.4. Allocation/Randomisation

### 4.4.1. Randomisation Procedures

Once screening procedures have confirmed the participant's eligibility to enter the trial/study and the participant has provided informed consent, the process of randomisation can commence.

The participants will be 1:1 randomised using REDCAP (an automated process) after screening confirmation and consent, this process is immediate and will be done whilst the participant is undergoing baseline measurements (as defined below). This is done by the member of the research team undertaking the screening and consent (e.g. the research assistant). As the trial cannot be blinded there is no code break. Once the participant has been successfully randomised in VECTOR, the enrolment of this participant must be documented within an enrolment log.

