## 6.3. Data Analysis

All analyses of the intervention-based data will be performed on an intention to treat basis.

To determine the effects of the intervention on all of the outcome measures, differences in the changes from baseline to after the 6 week intervention between the two groups will be examined using linear mixed effects models with group modelled as a fixed factor and random intercepts by participants adopted. For linear mixed models the mean difference between groups in change from baseline to after the 6 week intervention and 95% confidence intervals of the difference will be presented.

Effect sizes and their associated 95% confidence intervals will also be calculated for the changes from baseline to after the 6 weeks of intervention between the two groups, using Cohen's d, in accordance with McGough, & Faraone. Cohen's d values will be interpreted as 0.2 = small, 0.5 = medium, and 0.8 = large .

Analyses will be conducted in SPSS (IBM, SPSS, V28). The flow of participants through each stage of the trial will be presented in a CONSORT diagram. Descriptive statistics of means and standard deviations will be used to characterise the groups at baseline and differences between the two groups

will be presented in the form of an unadjusted mean difference for continuous outcomes, with their associated 95% confidence intervals.

In addition, Pearson chi-square tests of independence will be utilized to undertake bivariate crosstabulation comparisons between the two trial groups to test differences in the number lost to follow-up and the number of adverse outcomes in each group. Chi-squared probability values will be calculated using Monte Carlo simulation. All statistical analyses will be conducted using SPSS v28 (IBM, SPSS), with statistical significance accepted at the  $P \leq 0.05$  level.

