## 11. Data Protection and Participant Confidentiality

### Confidentiality

The Investigator has a responsibility to ensure that participant anonymity is protected and maintained. They must also ensure that their identities are protected from any unauthorised parties. Information with regards to study participants will be kept confidential and managed in accordance with the Data Protection Act, NHS Caldicott Guardian, The Research Governance Framework for Health and Social Care and Research Ethics Committee Approval.

Patient identifiable information shared across the research team is limited to name, email address and phone number. Hospital number and date of birth is collected on CRFs at the NHS site - but pseudo-anonymised with a patient research number. Only members of the research team will have access to this information.

The CI is custodian of the data.

The participants can withdraw at any stage, but any data collected up until the point of the withdrawal will still be used within the study. The patients will be asked for a preference of contact details and can withdraw this at anytime by informing the research team.

All data will be anonymised within any publications or dissemination of findings. The CI is the data controller and the research teams both on NHS site and at the University of Hertfordshire are the data handlers. The responsibility for data quality is described above. DPIAs will be completed for each NHS site with the University of Hertfordshire.

**Case Report Form (CRF)** forms are visit specific and are completed by the research assistant or member of the research team undertaking that particular visit parameter.

The Baseline and exit CRFs will record the data as described above

The WBV CRFs will confirm the number of WBV 60 seconds undertaken and confirmation of the lifestyle education delivery.

It will also confirm any AEs during the WBV intervention.

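### The protocol does not fix which non-serious adverse events enter the between-arm comparison, and one candidate set is filtered by open-label attribution

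*Protocol*

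**What the plan says.** Four places in the protocol bear on this.

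- **Section 5, Safety.** "A clinical co-investigator will be responsible for determining the causality and seriousness of adverse events". The same sentence adds "all non-serious adverse events that are either deemed to be related to participation in the research or result in withdrawal from the WBV programme", and continues so that withdrawal from the study also qualifies. The next paragraph sets no relatedness condition: "Non-serious events are defined as any untoward medical occurrence that does not fulfil any of the serious adverse event criteria". Reporting is referred to a document that is not shown: "Adverse event reporting will be conducted in accordance with the Sponsor's Adverse Event Reporting Procedures".
- **Section 11, Case Report Form.** Of the WBV form it says: "It will also confirm any AEs during the WBV intervention". No matching adverse-event entry is described for the control arm's weekly remote sessions, and the data list in Section 6.1 has no adverse-event item for either arm.
- **Section 6.3, Data Analysis.** Pearson chi-square tests are to "test differences in the number lost to follow-up and the number of adverse outcomes in each group". The section does not say which events these are, or whether the unit is the event or the participant.
- **Section 4.4.1, Randomisation Procedures.** "As the trial cannot be blinded there is no code break". No masked assessment of causality is described anywhere.

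**The concern.** Everyone enrolled has active Crohn's disease (partial Harvey Bradshaw Index 5 to 16, Section 3.3), so looser stools or abdominal pain during the six weeks are easily put down to the disease. Section 2.1 asks whether WBV affects disease activity, so this is a harm the trial should be able to see.

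Randomisation allows an all-cause comparison to answer the causal question without anyone judging individual cases. If events are first selected by whether someone who may know the allocation thinks them related, that protection is lost. WBV could look safer than it is if its flares are called background disease. It could look more harmful if staff readily blame the vibration plate while nobody blames an online education session.

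Capture may differ too. The WBV arm has 18 supervised sessions with a form that asks about adverse events. The control arm has six remote sessions with no such form described (Section 4.6).

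**Working it through.** **Step 1: follow one event through the text.** Take a non-serious episode of abdominal pain that is judged to be due to Crohn's disease and does not lead to withdrawal.

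| | WBV arm | Control arm |
|---|---|---|
| In the set singled out by Section 5? | No | No |
| On a session form described in Section 11? | Yes | No form described |
| In the Section 6.3 count? | Not stated | Not stated |

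The count could therefore be the filtered set, everything recorded (with capture described for one arm only), or something set by the sponsor's procedure. These give different tests.

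**Step 2: inputs for an illustration.** The protocol gives no adverse-event rate and no power for safety, so there is no stated figure to reproduce. From the protocol: 168 participants randomised 1:1, so 168 / 2 = 84 per arm, and a significance level of 0.05 (taken as two-sided). Assumed: the true event rate r in each arm and the share a of events deemed related. Events that re-enter through withdrawal are ignored.

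**Step 3: method.** Let X ~ Bin(84, r_W × a_W) and Y ~ Bin(84, r_C × a_C) be the participants counted in the WBV and control arms, and let p = (X + Y)/168. The Pearson statistic is ((X − Y)/84)² / [p(1 − p) × 2/84]. The probability of significance is the sum of the joint probabilities over all pairs (X, Y) with a statistic of at least 3.84.

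**Step 4: equal true rates, unequal attribution (50% WBV, 10% control).**

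| True rate, both arms | Expected count, WBV | Expected count, control | P(significant), filtered | P(significant), all counted |
|---|---|---|---|---|
| 10% | 84 × 0.10 × 0.5 = 4.2 | 84 × 0.10 × 0.1 = 0.8 | 31% | 5% |
| 20% | 84 × 0.20 × 0.5 = 8.4 | 84 × 0.20 × 0.1 = 1.7 | 60% | 5% |
| 30% | 84 × 0.30 × 0.5 = 12.6 | 84 × 0.30 × 0.1 = 2.5 | 81% | 5% |

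Reversing the two shares gives the same probabilities with the sign turned round.

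Section 6.3 says that p-values will come from Monte Carlo simulation. Taking that as the distribution with fixed margins, I replaced the 3.84 cut-off by the exact hypergeometric p-value of the same statistic. The filtered probabilities become 13%, 47% and 74%, against about 3% with all counted. The test is more conservative at small counts, but the distortion remains.

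**Step 5: a real difference hidden.** With true rates of 25% (WBV) and 10% (control), counting all events detects the difference with probability 74% (3.84 cut-off). If 20% of WBV events but 50% of control events are deemed related, the counted rates are 0.25 × 0.2 = 5% and 0.10 × 0.5 = 5%. The probability of significance falls to 4%.

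**Step 6: equal attribution.** With the same 25% and 10%, and the same share attributed in both arms, detection falls from 74% to 41% (half attributed), 19% (a quarter) or 7% (a tenth). This is lost power from fewer events, not bias.

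**The case against.** The strongest reply is that Section 5 states no counting rule. Its first clause gives the co-investigator causality and seriousness for adverse events without restriction. The second clause adds a subset in a sentence that lacks a verb for it. Nothing says that other non-serious events go unrecorded or uncounted, and the WBV form points the other way. This stands. A reader might infer that unrelated events are excluded from the safety comparison, or that relatedness must be settled before the review that determines it. The text allows both readings but establishes neither.

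A reader might also infer that the withdrawal route is open to the WBV arm only. It is not, because withdrawal from the study also qualifies. The remaining asymmetry is narrow: a control participant who stops the education sessions because of an event but stays in the study.

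Worsening is also captured elsewhere. The serious-event criteria include one that "requires unplanned or prolonged hospitalization", with no relatedness condition. Partial Harvey Bradshaw Index, faecal calprotectin and CRP are measured before and after in both arms (Sections 2.1 and 6.1). This also stands, but two time points miss a flare that resolves in between, and they miss anyone without an exit visit.

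The sponsor's procedure or a statistical analysis plan may define the count. The definition alone could properly be left there. Collection is different: no later plan can recover events that were not recorded, or were recorded differently in the two arms.

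Finally, Section 5 does not say who deems an event related, or whether that person knows the allocation. Open-label judgement is inferred from the trial being unblindable and from the absence of any masked assessor.

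**Conclusion.** The point holds as an unresolved inconsistency between Sections 5, 6.3 and 11. It does not show that the protocol discards Crohn's worsening. If the filtered set feeds the chi-square test, non-serious events judged unrelated and not causing withdrawal drop out, and the comparison depends on attribution that can differ by arm.

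On the assumed rates and shares, that gives falsely significant differences 31% to 81% of the time (13% to 74% with fixed-margin p-values), or can reduce a 74% chance of detecting a real excess to 4%. These figures show direction and scale only. They are not estimates for this trial, and a smaller gap in attribution would do less. The fall in detection under equal attribution should not be read as evidence of bias.

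The gap is confined to non-serious events without withdrawal. Because the correction is cheap and changes what the planned test can conclude, it is worth making.

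**What to change.** Reconcile the three sections.

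- **Section 5:** state that all adverse events are recorded in both arms, in the same way and over the same period, regardless of relatedness, and that the clinical co-investigator assesses seriousness and causality for each. Word the withdrawal criterion to cover the allocated programme in either arm, or the study.
- **Section 11:** describe the same adverse-event entry for the control arm's contacts as for the WBV sessions.
- **Section 6.3:** define the tested quantity as participants with at least one adverse event of any cause, with related events shown separately.

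The cost is protocol wording, a form entry for control contacts and modest extra review time. The small downside is more minor events to record and review.

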### 6. Data Collection, Management and Analysis

#### 6.1. Data Collection

Data to be collected (\*pre intervention and post intervention, +data taking once, then using pseudoanonymised number in the database):

- +Name
- +Contact details
- +Age
- +Gender

- \*Weight
- \*Height
- \*Resting blood pressure
- \*Heart rate variability
- \*Harvey Bradshaw Index (partial)
- \*EMG
- \*Blood TNFalpha, IL10, IL12, IL23, TGF-beta, IL6, IL17, CRP, P1NP
- \*Faecal calprotectin x 2 via their gastroenterologist
- \*HADs
- \*IBD-Q
- \*IBD-F
- \*7 day pain perception
- \*7 day level of physical activity engagement
- \*Cardiorespiratory fitness (sub maximal Chester Step Test)

## 6.2. Data Management

Essential Trial documentation (i.e. the documents which individually and collectively permit evaluation of the conduct of a clinical trial and the quality of the data produced) will be kept with the Trial Master File and Investigator Site Files. The Sponsor will ensure that this documentation will be retained for a minimum of five years after the conclusion of the trial to comply with standards of Good Clinical Practice. Case report forms will be stored for a minimum of five years after the conclusion of the trial as paper records, and a minimum of 20 years in electronic format. All paper records will be stored in a secure storage facility or off-site by the University of Hertfordshire. All electronic records will be stored on a password protected server.

## 6.3. Data Analysis

All analyses of the intervention-based data will be performed on an intention to treat basis.

To determine the effects of the intervention on all of the outcome measures, differences in the changes from baseline to after the 6 week intervention between the two groups will be examined using linear mixed effects models with group modelled as a fixed factor and random intercepts by participants adopted. For linear mixed models the mean difference between groups in change from baseline to after the 6 week intervention and 95% confidence intervals of the difference will be presented.

Effect sizes and their associated 95% confidence intervals will also be calculated for the changes from baseline to after the 6 weeks of intervention between the two groups, using Cohen's d, in accordance with McGough, & Faraone. Cohen's d values will be interpreted as 0.2 = small, 0.5 = medium, and 0.8 = large .

Analyses will be conducted in SPSS (IBM, SPSS, V28). The flow of participants through each stage of the trial will be presented in a CONSORT diagram. Descriptive statistics of means and standard deviations will be used to characterise the groups at baseline and differences between the two groups

will be presented in the form of an unadjusted mean difference for continuous outcomes, with their associated 95% confidence intervals.

In addition, Pearson chi-square tests of independence will be utilized to undertake bivariate crosstabulation comparisons between the two trial groups to test differences in the number lost to follow-up and the number of adverse outcomes in each group. Chi-squared probability values will be calculated using Monte Carlo simulation. All statistical analyses will be conducted using SPSS v28 (IBM, SPSS), with statistical significance accepted at the  $P \leq 0.05$  level.

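### Adverse outcomes and loss to follow-up are compared between arms only by a chi-square P-value, with no estimate or interval; at rates of about 10% or less that test has under 50% power for a doubling

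*Protocol*

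**What the plan says.** Section 6.3 (Data Analysis) of the protocol names one between-arm analysis for harms and attrition. It states that "Pearson chi-square tests of independence will be utilized to undertake bivariate crosstabulation comparisons between the two trial groups" and that the purpose is "to test differences in the number lost to follow-up and the number of adverse outcomes in each group". It then fixes how the P-value is obtained, "Chi-squared probability values will be calculated using Monte Carlo simulation", and the threshold, "with statistical significance accepted at the" P ≤ 0.05 level.

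The same section treats continuous outcomes differently. For the mixed models, the mean difference in change is reported and "95% confidence intervals of the difference will be presented". Cohen's d also comes with an interval. Baseline group differences "will be presented in the form of an unadjusted mean difference for continuous outcomes, with their associated 95% confidence intervals". None of these provisions covers a binary comparison.

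For attrition there is one descriptive element: "The flow of participants through each stage of the trial will be presented in a CONSORT diagram".

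The Trial/Study Summary gives the planned size as 168, and section 4.4.1 says "The participants will be 1:1 randomised using REDCAP". The protocol gives no expected rate of adverse events or drop-out, and no power for either comparison.

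**The concern.** A test of no difference answers whether chance alone could explain the observed imbalance. For harms, the useful question is how large an excess the data still allow, and only an estimate with an interval answers that. Section 1 presents this as the first study of whole body vibration (WBV) as a possible adjunct therapy in Crohn's disease, so later readers will look here for that information.

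The same applies to drop-out. The primary comparison on IBD-Q is by intention to treat, and unequal loss to follow-up can bias it. A non-significant chi-square is weak reassurance if the test had little chance of finding a real imbalance.

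This is not simply a detail left for a statistical analysis plan. The protocol selects the test, the P-value algorithm and the threshold, and in the same section specifies intervals for the other outcome type.

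**Working it through.** **Inputs**
- Sample size 168 (Trial/Study Summary), randomised 1:1 (section 4.4.1): 168 / 2 = 84 per arm.
- Test: Pearson chi-square, Monte Carlo P, threshold 0.05 (section 6.3). Sidedness is not stated; the statistic is non-directional, so it is taken as two-sided.
- Event and drop-out rates: not in the protocol. **Assumption**: lower-arm rate varied from 5% to 25%, with the other arm at double that rate.

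The protocol states no power for these comparisons, so there is no figure to reproduce.

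**Step 1: normal approximation.** With n per arm, rates p1 and p2, d = p2 − p1 and p̄ = (p1 + p2)/2:

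power = Φ{ [d√n − 1.96√(2p̄(1 − p̄))] / √(p1(1 − p1) + p2(1 − p2)) }

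For 10% v 20%: d√n = 0.10 × 9.165 = 0.917; 1.96 × √(2 × 0.15 × 0.85) = 0.990; denominator √(0.09 + 0.16) = 0.500. Power = Φ(−0.147) = 0.44.

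**Step 2: full enumeration.** Sum the product of the two binomial probabilities (n = 84 each) over all tables with P ≤ 0.05. This is done once with the ordinary Pearson P and once with the conditional exact P of the same statistic, which a Monte Carlo P approximates.

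| Assumed rates | Normal approx. | Pearson P | Monte Carlo / exact P |
|---|---|---|---|
| 5% v 10% | 23% | 22% | 15% |
| 10% v 20% | 44% | 44% | 37% |
| 12% v 24% | 53% | 54% | 45% |
| 14% v 28% | 61% | 62% | 54% |
| 15% v 30% | 65% | 66% | 58% |
| 20% v 40% | 81% | 82% | 77% |
| 25% v 50% | 92% | 92% | 90% |

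Power for a doubling passes 50% at a lower-arm rate of about 11% (Pearson) or 13% (Monte Carlo). For 80% power by the normal approximation, 5% v 10% needs 435 per arm, 10% v 20% needs 199 and 20% v 40% needs 82.

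**Step 3: cost of the Monte Carlo P.** Under no difference, the enumerated rejection rate is 4.2% (Pearson) v 1.7% (Monte Carlo) at a 5% rate, and 5.0% v 2.9% at a 10% rate. The chosen algorithm is conservative here, which explains the lower power in the last column.

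**Step 4: what an interval adds.** Take an illustrative 16/84 v 8/84.
- Pooled rate 24/168 = 0.143; z = 0.0952 / √(0.143 × 0.857 × 2/84) = 1.76; chi-square 3.11, below 3.84; P = 0.078. The conditional exact P is 0.121.
- Risk difference 19.0% − 9.5% = 9.5 points. Wilson limits are 12.1% to 28.7% and 4.9% to 17.7%.
- Newcombe lower limit: 0.0952 − √[(0.1905 − 0.1208)² + (0.1768 − 0.0952)²] = −0.012.
- Newcombe upper limit: 0.0952 + √[(0.2872 − 0.1905)² + (0.0952 − 0.0491)²] = 0.202.

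The planned output would be P = 0.12. The interval, −1.2 to 20.2 points, shows that an excess of about 20 points is not excluded.

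**The case against.** The strongest reply has four parts.

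**Rates.** A reader might infer that this test would usually miss a doubling of harm or drop-out. The documents do not support that, because they state no rate. The low power holds only below a lower-arm rate of about 11% to 13%; at 20% v 40% the doubling is found about four times in five. Muscle soreness, the risk named in section 8.2, could be common. This stands, and the point is limited accordingly.

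**Reporting.** A reader might also infer that a non-significant result will be reported as safe or as no difference. The protocol says neither. No decision depends on these tests, a clinical co-investigator judges seriousness and causality (section 5), and the CONSORT diagram will show drop-out counts. This also stands, but none of it supplies an estimate of the between-arm difference with its uncertainty.

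**Counting unit.** The phrase about the number of adverse outcomes might be read as a test on event totals, with repeats in one person treated as independent and the false-positive rate inflated. A cross-tabulation test of independence, listed beside loss to follow-up, points rather to participants. Any size given to that inflation would rest on assumed event frequencies. What remains is an ambiguity that a word would remove.

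**Place in the plan.** Comparative safety is not a listed objective, chi-square comparisons are conventional, and an unseen statistical analysis plan may add intervals; section 6.3 does not forbid them. That limits the point to this document. It does not remove it, since the protocol has already fixed a P-value method and threshold for these outcomes.

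**Conclusion.** The point holds in a limited form. As far as this document goes, harms and attrition are compared between arms by a P-value alone, while continuous outcomes get intervals. At 84 per arm, if the lower-arm rate is about 10% or less, power to detect a doubling is under 50% by either P-value method (15% to 22% for 5% v 10%; 37% to 44% for 10% v 20%). In that range, a non-significant result says little about excess harm or unbalanced attrition. At 20% v 40% power is 77% to 82%, and the low-power argument does not apply.

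This rests on three assumptions: the rates, which are not in the protocol; one classification per participant; and all 84 per arm in the denominator. The absence of an estimate and interval does not depend on any of them.

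**What to change.** In section 6.3, replace the chi-square sentences with text to this effect:

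*For loss to follow-up and for adverse events, the number and percentage of participants affected (for adverse events, those with at least one) will be given by arm, with the risk difference and its 95% confidence interval (for example, Newcombe's method). Total event counts will be given by arm descriptively. Any chi-square P-value is secondary, and P > 0.05 will not be taken as evidence of similar safety or balanced attrition.*

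This also settles that participants are counted.

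The cost is a few lines of protocol text and one short calculation per comparison. It needs no extra participants, visits or procedures. The small downside is a less reassuring safety statement, because the interval may show that a sizeable excess cannot be excluded.

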## 2. Aims and Objectives

### 2.1. Trial/Study objectives

- The primary objective, or principal research question is does WBV exercise improve health related quality of life (HRQoL) for patients with Crohn's disease.
- Secondary Objective: The secondary research questions are:
  - ! Does WBV improve general cardiovascular health from baseline in Crohn's patients?
  - ! Is Crohn's disease activity impacted by WBV?
  - ! Does WBV in Crohn's patients significantly alter their blood markers of inflammation?
  - ! Does WBV alter bone health markers in CD patients?
  - ! Does WBV impact on subjective perception of fatigue, or objective measurement of neuromuscular fatigue?
  - ! Does WBV impact on perception of pain in CD patients?
  - ! Does WBV impact on markers of anxiety or depression in this population?

- 
- Primary End Point: the primary end point is an improvement in the IBD-Q - with an objective improvement of 16 points.
- Secondary End point: The secondary end points are:
  - ! Improvement in heart rate variability, resting blood pressure or sub maximal Chester step test
  - ! A static or improved partial Harvey Bradshaw index and faecal calprotectin
  - ! A significant delta in blood TNF- $\alpha$ , IL-6, IL-17A, IL12/IL-23, IL-10, TGF- $\beta$ , C-Reactive protein between the beginning and end of the study
  - ! An improvement in serum P1NP
  - ! The difference between subjective fatigue at the start and end of study, as well as a difference in objective neuromuscular fatigue between the start and end of the study
  - ! Obtaining granularity of patients thoughts, experience and feelings towards WBV as an intervention for the adjunct management of Crohn's disease

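### A P ≤ 0.05 rule for every analysis, with an end point met by any significant inflammatory marker, leaves secondary significance claims with a false-positive rate well above 5%

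*Protocol*

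**What the plan says.** Protocol section 2.1 names one primary end point: "the primary end point is an improvement in the IBD-Q - with an objective improvement of 16 points". It then poses the secondary objectives as yes/no questions about WBV. One asks "Does WBV in Crohn's patients significantly alter their blood markers of inflammation", another "Does WBV alter bone health markers in CD patients".

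The matching blood-marker end point in 2.1 is a statistically significant change in TNF-α, IL-6, IL-17A, IL-12/IL-23, IL-10, TGF-β and C-reactive protein. It gives no direction, and does not say whether one marker, several or all must change. Section 6.1 lists IL-12 and IL-23 separately: "Blood TNFalpha, IL10, IL12, IL23, TGF-beta, IL6, IL17, CRP, P1NP". The panel is therefore 7 or 8 inflammatory markers, with P1NP as a separate bone marker.

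Section 6.3 opens its model description with "To determine the effects of the intervention on all of the outcome measures, differences in the changes from baseline" to the end of the 6-week intervention, compared between the two groups. It adds that "95% confidence intervals of the difference will be presented", and plans Cohen's d with 95% intervals. It ends: "All statistical analyses will be conducted using SPSS v28 (IBM, SPSS), with statistical significance accepted at the" P ≤ 0.05 level. That sentence is not confined to the primary outcome. The protocol gives no order among the secondary outcomes and does not describe them as supportive or exploratory.

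**The concern.** The protocol states a rule here; it does not merely leave a gap. Read together, 6.3 and 2.1 let each secondary outcome carry its own claim of significance at 0.05. For the inflammation question, a single significant marker moving either way can be read as a yes. The threshold then holds the error rate of each test at 5%, but not the error rate of the answer to the question.

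Section 1 describes this as the first study of WBV as an adjunct in Crohn's disease. An isolated cytokine, bone, fatigue or pain result could be reported as a significant effect of WBV under the protocol's own wording, even with no difference in IBD-Q. What is at stake is how secondary results are interpreted, not the primary conclusion.

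**Working it through.** The protocol states no family-wise error rate and no number of secondary tests, so there is no figure of its own to reproduce. The sample size of 168 does not enter the calculation.

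**Inputs from the protocol**
- Threshold: P ≤ 0.05 per test (6.3). Sidedness is not stated; I take two-sided, consistent with the 95% intervals.
- Test: the between-arm comparison in 6.3, applied to every outcome.
- Secondary end points in 2.1: heart rate variability, resting blood pressure and step test (3); partial Harvey Bradshaw Index and calprotectin (2); inflammatory markers (7 or 8); P1NP (1); questionnaire fatigue and EMG fatigue (2). The sum is 15 or 16.
- Pain and HADS appear in 2.1 as secondary questions only. Adding them gives 17 or 18.

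**Assumption.** The protocol gives no correlations between outcomes. I use a common correlation ρ between normal test statistics and show 0 to 0.8.

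**Formulas, with no true effect on any outcome and k tests**
- Either direction, independent: 1 − 0.95^k. For k = 8: 1 − 0.95^8 = 0.337. For k = 18: 1 − 0.95^18 = 0.603. Expected false positives at k = 18: 18 × 0.05 = 0.9.
- Favourable direction only, independent: 1 − 0.975^k. For k = 18: 1 − 0.975^18 = 0.366.
- Correlated: write each statistic as √ρ·C + √(1−ρ)·E, with C shared and E separate for each outcome. Given C = c, the tests are independent. The either-direction chance is 1 − ∫ φ(c)·[Φ((1.96 − √ρ·c)/√(1−ρ)) − Φ((−1.96 − √ρ·c)/√(1−ρ))]^k dc. For favourable only, drop the second Φ term, with every outcome oriented so that benefit is positive.

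**Chance of at least one false positive**

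| Tests | ρ = 0 | ρ = 0.3 | ρ = 0.5 | ρ = 0.8 |
|---|---|---|---|---|
| 7 markers, either direction | 0.30 | 0.27 | 0.23 | 0.15 |
| 8 markers, either direction | 0.34 | 0.30 | 0.25 | 0.16 |
| 15 outcomes, either direction | 0.54 | 0.46 | 0.36 | 0.20 |
| 18 outcomes, either direction | 0.60 | 0.51 | 0.40 | 0.22 |
| 15 outcomes, favourable only | 0.32 | 0.23 | 0.18 | 0.10 |
| 18 outcomes, favourable only | 0.37 | 0.26 | 0.20 | 0.11 |

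A common correlation is crude, so a block structure was also simulated for 18 tests: 7 inflammatory markers, 3 cardiovascular measures, 4 patient-reported scores (HADS counted as two) and 4 independent outcomes. With within-block correlations of 0.3 to 0.5 the either-direction chance is 54%; with 0.5 to 0.7 it is 49%.

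For the 8 inflammatory markers, 0.16/0.05 = 3.2 and 0.34/0.05 = 6.7, so the error rate is about three to seven times the nominal 5%. The direction-free count fits this end point, because 2.1 states no direction for it.

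**The case against.** The strongest objection is that handling of secondary multiplicity is commonly left to the SAP, which may exist and is not shown. That stands: the lack of an adjustment method is not an error here. It does not dispose of the point, because 6.3 fixes a threshold for all analyses and 2.1 writes significance into an end point. A SAP that confined significance claims to IBD-Q would have to depart from both.

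Several stronger readings are tempting, and the documents do not support them.
- A reader might infer that a false positive is more likely than not. That needs low correlation among outcomes measured in the same patients. It is near even under the block structures and well below one half at higher common correlation.
- A reader might infer that there is no hierarchy at all. Section 2.1 does separate one primary end point from the rest; what is missing is any order among the secondaries.
- A reader might take the either-direction rates as rates of false benefit. Favourable errors alone are roughly half as frequent.
- A reader might infer that a secondary result is meant to stand in for a null primary. No section says so.

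The count is also not exact. Pain and HADS are not listed end points, IL-12/IL-23 may be one item or two, and the Harvey Bradshaw Index and calprotectin end points also count no change as success, so a significant difference is not their criterion. The inflammation-panel result depends on none of this except whether the panel has 7 or 8 markers. Finally, the planned estimates and 95% intervals lessen the reliance on P values, although the significance rule still stands beside them.

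**Conclusion.** The point holds as a fault in the wording of 2.1 and 6.3, and is worth correcting. It is firmest for the inflammation panel: with 8 markers and no effect of WBV, a false yes has a chance of about 16% to 34%, and with 7 markers about 15% to 30%. Across 15 to 18 secondary outcomes the chance of at least one false positive is roughly 20% to 60% in either direction, or 10% to 37% in the favourable direction. These figures assume two-sided tests at 0.05, approximately normal test statistics, no true effect on any outcome, and correlations between 0 and 0.8 that the protocol does not supply. All of them exceed 5%. The IBD-Q test is a single comparison and its error rate is not touched.

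**What to change.** In section 6.3, limit claims of a significant treatment effect to the between-arm difference in IBD-Q. State that secondary outcomes are supportive and will be interpreted from the estimates and unadjusted 95% confidence intervals already planned. Leave the chi-square comparisons of loss to follow-up and adverse outcomes as they are; removing the threshold from all analyses except the primary would take it from these too, which is not intended.

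In section 2.1, reword the blood-marker question and its end point so that both aim to estimate the between-arm difference in each marker, without the word significant. If the sponsor wants a formal claim on the inflammation panel, name the markers and adjust across them, for example by Holm. With 8 markers the smallest P value would then be compared with 0.05/8 = 0.00625.

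This changes a few sentences and needs no patients, visits or data. Allocation is open (section 4.4.1), so it should be settled before any comparison of the arms is seen. The downside is that an isolated secondary P value below 0.05 can no longer be reported as a significant effect of WBV.
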